#### Composition of the data monitoring committee, its role, and reporting structure

The need for a data monitoring committee is not considered.

#### Frequency and plans for auditing trial conduct

There are no plans for auditing trial conduct in this investigator-initiated pragmatic trial.

#### Plans for communicating important protocol amendments to relevant parties (e.g., trial participants and ethical committees)

This clinical trial will be conducted according to the ethical committee guidelines. Any problem or protocol modifications during the trial will be communicated to the ethical committee, trial participants, trial registries, journals, and regulators in a timely manner. Ethical committee’s consent will be required to change the protocol.

### Safety evaluation

General safety evaluations will be based on the incidence and type of adverse events (AEs). Safety variables will be tabulated and presented for all patients in the safety set. Adverse events will be coded using World SIVA adverse sedation event reporting tool. The number (%) of subjects with any AEs will be summarized. Probiotics, as beneficial bacteria in the human body, are generally well-tolerated. To date, there has been no evidence that this study may cause any risk or discomfort to participants. However, any harm from the intervention will still be evaluated. Any adverse events, including those voluntarily provided by subjects or obtained through physical examination, laboratory examination, or other examination methods, will be recorded on CRFs and actively handled. We will record any adverse events that occur during the clinical trial, regardless of whether these events were associated with the intervention. Furthermore, all these expected and unexpected trial-related adverse events will be reported in trial publications. A close follow-up will be done until remission or stable condition.

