### Eligibility criteria

The inclusion/exclusion criteria are summarized in Table 1.

**Table 1 Tab1:** Inclusion/exclusion criteria

Inclusion criteria	Exclusion criteria
1) Age is greater than or equal to 65 years old 2) Can communicate normally 3) Elective knee ankle, hip replacement, or lumbar open reduction and internal fixation under general anesthesia 4) ASA graded at I–II level 5) Patient or family informed consent	1) Have a brain disease, or have a history of brain disease 2) MMSE check of less than 24 points 3) History of neurological and psychological disorders including AD, stroke, psychosis 4) Serious hearing or visual impairment 5) Preoperative systolic blood pressure > 190 mmHg, or diastolic blood pressure > 100 mmHg 6) The patient or family refuses

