### Interventions

Figure 1 shows the schedule of major study events for each visit. Elderly patients planning to undergo orthopedic surgery will be included in this study. The surgery will be performed within 2 days after screening. The drug will be used a day before operation until 6 days postoperatively. The probiotic group will be treated with Peifeikang (Bifidobacterium triple viable powder, 210 mg per capsule), while the control group will be treated with placebo in the same package. The drug will be taken orally, four capsules at a time, twice a day, and the postoperative cognitive function will be evaluated using a neuropsychological test. If participants request to withdraw from the trial, we will discontinue the allocated intervention for the given trial participants. Adherence to interventions primarily refers to patient self-management adherence. No concomitant care or interventions will be permitted during this trial.

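### Adverse events are to be coded with a tool named for sedation events, which does not fit this probiotic trial and would leave the tabulation by type poorly classified

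*Protocol article*

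**What the plan says.** All of the rules on coding and summarizing adverse events stand in the Safety evaluation section of the protocol article.

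- Basis of the evaluation: "General safety evaluations will be based on the incidence and type of adverse events (AEs").
- Coding: "Adverse events will be coded using World SIVA adverse sedation event reporting tool". No other coding system is named anywhere in the document.
- Summary: "The number (%) of subjects with any AEs will be summarized".
- Presentation: "Safety variables will be tabulated and presented for all patients in the safety set".
- Scope: "We will record any adverse events that occur during the clinical trial, regardless of whether these events were associated with the intervention". Events may be volunteered or found on physical, laboratory or other examination, and they "will be recorded on CRFs and actively handled".

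Two other sections set the context. Under Interventions, "The drug will be used a day before operation until 6 days postoperatively", and the product is an oral capsule of live bacteria or a matching placebo. Table 1 under Eligibility criteria admits patients aged 65 or over for elective joint replacement or "lumbar open reduction and internal fixation under general anesthesia".

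**The concern.** A coding system decides which rows the adverse event table has. It should therefore cover the range of events that the product, the procedure and the collection rule can produce. Here the named instrument announces a narrow purpose, adverse events of sedation, while the collection rule is as wide as it can be. No sedative is under study, and the document does not mention sedation anywhere else.

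What is at stake is the *type* half of the safety evaluation. A count of subjects with any adverse event is a blunt measure after major surgery: many patients may have some procedural event, and an imbalance in one kind of event can be lost in the total. The protocol's own Discussion speaks of postoperative infection, intestinal bacterial overgrowth and surgical complications when it reviews perioperative probiotics. Those are the kinds of event a reader would want to see by arm, and none of them is by nature a sedation event.

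**Working it through.** The protocol gives no figure on this point, so there is nothing to reproduce. The check sets the coding rule beside what it has to cover.

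1. **Instrument.** The Safety evaluation section names one tool, and its title limits it to sedation events. The document does not list the tool's categories or say whether it has an *other* or free-text field.

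2. **Product.** Under Interventions, the trial drug is oral live bacteria, not a sedative.

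3. **Exposure period.** Dosing starts 1 day before surgery and ends 6 days after it. Counting the day of surgery, that is 1 + 1 + 6 = 8 days. Most of this period lies outside the operation itself.

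4. **Setting.** Table 1 requires general anesthesia. Sedation is neither the intervention nor the stated anesthetic technique.

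5. **Events to be coded.** The Safety evaluation section takes in all events from every source, whatever their cause. This set is much wider than sedation events.

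6. **Which outputs need the code.**
   - Number (%) of subjects with any adverse event: needs only a yes or no per subject, so it is unaffected.
   - Membership of the safety set (Data selection for statistical analysis): at least one dose received, so it is unaffected.
   - Capture on the case report form: comes before coding, so it is unaffected.
   - Serious adverse events: the Consent section requires immediate reporting whether or not the event is related, and the Blinding section has them recorded for further analysis. Neither depends on the tool.
   - Adverse events by type: depends wholly on the code, and the sedation tool is the only route given. **Affected.**

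Steps 1 to 5 show that the rule does not match the data it governs. Step 6 shows that the effect falls on one output only.

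**The case against.** The strongest reply is that coding comes after capture. Every event is on a case report form, so a poor scheme loses nothing, and events can be recoded before the database is locked. The one adverse event summary that is spelled out needs no type coding, and serious events have their own reporting route. The tool's contents are not shown, so the mismatch is inferred from its name and the setting.

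All of this is correct, and it limits the consequence. It does not remove the defect. Recoding in another system would depart from the stated rule, so the rule itself has to change. Nor is this a detail left to an analysis plan: the protocol makes a positive statement, and an analysis plan naming a different dictionary would contradict it.

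A reader might be tempted to go further in four ways that the document does not support.

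- *The safety data will be unusable, or the arms cannot be compared.* Capture is complete by design and the coding can be corrected. The protocol states tabulation only, with no between-arm test of event types.
- *Nearly all events will go unclassified.* This needs the tool's categories, which are not given.
- *The 95% upper bound with no events among 110 patients, 3/110 = 2.7%, shows how serious this is.* That bound depends on the sample size alone and would be the same under any dictionary. It does not measure the coding problem.
- *The absence of a data monitoring committee makes it worse.* Nothing in the document makes the choice of a coding dictionary such a committee's task.

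**Conclusion.** The point holds in a limited form. The only coding rule in the protocol names a tool that, by its title, is for sedation events. That does not fit a trial of oral live bacteria around orthopedic surgery in which every adverse event is collected. Followed as written, it would leave the tabulation by type poorly classified, and type is one of the two things on which safety is to be judged.

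The size cannot be computed from the document. Its reach can be stated: one output is affected, while event capture, the any-event count, serious event reporting, the sample size and the primary analysis are not.

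The conclusion assumes that the tool's name describes its purpose and that the tool has no general event classification which the protocol leaves unmentioned. If it had one, the point would shrink to a need to say so. The change is worth making: it corrects a stated safety rule at little cost, although it does not bear on the efficacy conclusion.

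**What to change.** Replace the coding sentence in the Safety evaluation section with one to this effect: the verbatim term of each adverse event is kept; each term is coded in a general medical dictionary (for example MedDRA, by system organ class and preferred term); this is applied to all events on the case report forms before database lock; and events are tabulated by arm in the safety set.

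Events already recorded need to be coded the same way, so that one system covers the whole trial. Coding should be done without knowledge of allocation, which the existing blinding arrangements already allow.

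The cost is a small coding effort, possibly a dictionary licence, and a protocol amendment, for which the article's section on communicating amendments requires the ethics committee's consent. No new data collection is needed. Further tables, for example by severity or relatedness, may be useful, but they belong in an analysis plan and are not needed to correct this sentence.

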### Provisions for posttrial care

If a participant suffers harm from this trial, he/she will receive free treatment.

### Dissemination plans

The study results will be disseminated via articles published in peer-reviewed journals.

### Plans to provide access to the full protocol, participant-level data, and statistical code

This section is not applicable as we have no plans to provide access to the full protocol, participant-level data, and statistical code.

### Plans for collection, laboratory evaluation, and storage of biological specimens for genetic or molecular analysis in this trial/future use

We have no plans to collect or store biological specimens in this trial.

## Discussion

In recent years, with the aging population, the proportion of elderly patients receiving hip joint and knee joint replacement has increased annually. Due to physiological deterioration, pathological changes, and respiratory, cardiovascular, cerebrovascular diseases, the tolerance of elderly patients to surgery and anesthesia has been greatly reduced. POCD has become a common neurological complication of hip fracture surgery in elderly patients [14]. The reported incidence of POCD varies greatly (9.9–46.1%) [3, 15–20]. Some studies reported that its actual incidence in elderly patients after hip arthroplasty ranges from 16 to 60% [21, 22]. Many studies confirmed that its incidence increases significantly with age, especially in > 65-year-old patients. Its incidence in elderly patients (> 65 years old) is 2–10 times that in young patients. In addition, its incidence in patients aged > 75 years is three times that in patients aged 65–75 years [17]. POCD may last for weeks, months, or years, and may delay recovery, prolong hospital stay, and even increase patient mortality [23, 24].

Intestinal flora is a complex microbial system that exists in human gastrointestinal tract and varies from person to person. It is involved in the regulation of multiple metabolic pathways, signal transduction, and immune inflammatory axis [25]. The microbial characteristics of the human gut at the age of 1 year may predict the cognitive function at the age of 2 years (especially in communication behavior). This may be associated with developmental disorders characterized by cognitive or language delays [26]. Although the body and brain have matured in the middle-aged and elderly, the diversity and stability of the gut microbiota will gradually decrease due to chronic progressive inflammatory reactions, drug use, degradation of digestion and gastrointestinal peristalsis, malnutrition, and decline in immunity during aging. At the same time, aging is accompanied by a decline in brain weight and cognitive function. Aging-related brain morphological changes are common in various aging-related cognitive impairment, such as Alzheimer’s disease [27].

There is increasing evidence that the intestinal microbiota plays a key role in neuropsychiatric diseases and central nervous system function through the gut microbiota-brain axis. In a recent report [28], an abnormal intestinal microbiota composition may be the basis of the mechanism of POCD and POD, indicating that the intestinal microbiota plays a key role in perioperative neurocognitive impairment. The gut-brain axis is a two-way communication system that regulates brain and gut functions [29]. It is well-known that the gut-brain axis consists of the central nervous system, central endocrine system, central immune system, and intestinal microorganisms, including the hypothalamus–pituitary–adrenal axis, sympathetic nervous system, parasympathetic nervous system (vagus nerve), and intestinal nervous system (ENS) of the autonomic nervous system. Signals from the gut can regulate certain brain regions, such as the insula (related to self-cognition), limbic system (related to emotional processing), prefrontal cortex (related to morality), amygdala (related to fear), hippocampus (related to memory), and anterior cingulate gyrus cortex (related to enthusiasm) [30–32]. A normal intestinal mucosal barrier has mechanical, chemical, immune, and biological components. It is composed of intestinal mucosal epithelium, intestinal mucus, intestinal microbiota, secretory immunoglobulin, and gut-associated lymphoid tissue. An abnormal intestinal microbiota is related to the occurrence of the following diseases: irritable bowel syndrome, autism, obsessive–compulsive disorder, and depression. The association between an abnormal intestinal microbiota composition and mental changes caused by these diseases involves the gut-brain axis [33, 34]. The intestinal microbiota changes significantly with age, with increasing proteolytic bacteria and decreasing glycolytic bacteria [35]. Age-related changes in diet, digestion, transport time, colonic pH, and salivary function will affect the intestinal microbiota [36].

Animal studies support the theory that the gut microbiota regulates cognitive symptoms [37], and changes in the gut microbiota are related to social avoidance and depression in mice [38]. Zhan [39] found that anesthesia and surgery induce cognitive dysfunction in male elderly mice, and 24 gut bacteria were significantly altered in mice with POCD compared with those without POCD in which 13 gut bacteria were significantly correlated with escape latency in the Morris water maze test. Yang [40] found that the administration of prebiotics could ameliorate POCD and attenuate surgery-induced neuroinflammation through the gut microbiota-brain axis in rats. Similar trials [11, 41, 42] proved that POCD is significantly associated with an abnormal gut microbiota composition, and abnormalities in specific gut bacteria may be involved in its pathogenesis.

A 2018 systematic review summarized the literature on intestinal microbiota changes associated with cognitive impairment, mild cognitive impairment (MCI), and dementia, evaluated the effects of prebiotics or probiotics on aging animal models and human cognitive symptoms and found that human data were insufficient to make any suggestions [37]. A systematic review of the effects of probiotics on depression published in 2016 showed positive conclusions. Three of these studies found improvements in the MMSE of elderly people taking probiotics [43–45], but all these studies involved participants with previous cognitive dysfunction. Hwang [46] conducted a randomized controlled trial to study the effect of probiotics on the cognition of participants with MCI (*n* = 100). A series of neurocognitive tests were done to assess their cognitive ability 12 weeks after taking a placebo or probiotics. A greater improvement in comprehensive cognitive function was found in the intervention group than in the placebo group (*P* = 0.02). In particular, the intervention group demonstrated a significant improvement in the field of attention. It was also reported [47] that the incidence of POCD in the probiotic group was significantly lower than that in the control group (3 of 59 patients [5.1%] vs. 10 of 61 patients [16.4%], *P* = 0.046).

In our animal experiment, the probiotic regimen of mice refers to the study by Rachmilewitz et al. [48], i.e., from 7 days before surgery to 10 days after surgery. Currently, clinical studies are mainly focused on major abdominal surgery. There is no uniformity in the preoperative administration plan of probiotics, which is given approximately 10 days before surgery or even after surgery [49–51]. These studies have proven that probiotics can effectively reduce postoperative infection rates, fight against intestinal bacterial overgrowth and clinical symptoms, and reduce postoperative complications and hospital stay duration [52]. There are few clinical studies on probiotics for POCD. Wang et al. [47] gave probiotics to patients who underwent noncardiac surgery from the time of admission to discharge and found that probiotics significantly improved postoperative cognitive impairment. In this study, our research participants are elderly patients who will undergo orthopedic elective surgery. As we can only receive official confirmation of a surgical operation 1 day before surgery, we set the preoperative administration route as oral 1 day before surgery. Furthermore, because the average hospital stay duration after surgery is 5–8 days, we set the administration time for patients after surgery as 6 days. Thus, we maximized the duration of oral administration of probiotics for hospitalized patients, which may benefit these patients.

Patients in our study need to receive routine antibiotic treatment, particularly cephalosporins, on the operation day and for 3 days after surgery. To avoid interference with the clinical work of surgeons, we did not limit the use of antibiotics after surgery. Previous studies have reported that probiotic treatment in the presence of antibiotics provides protection against postoperative infectious complications [53–55]. Thus, short-term antibiotic use (several days) is not an obstacle to perioperative probiotic administration. As this is a randomized controlled experiment, the difference in antibiotic treatment would be minimized due to randomization. However, perioperative probiotic treatment may provide improved protection against postoperative cognitive impairment in the absence of antibiotics.

We predict that the perioperative probiotics intervention will alleviate postoperative cognitive impairment in elderly patients undergoing orthopedic surgery. We aim to provide reliable clinical evidence for reducing the rate of postoperative cognitive impairment.

## Trial status

Trial registration: ClinicalTrials.gov, NCT04017403. Registered on Aug. 15, 2019. The protocol version is 1.2 which was approved on Dec. 15, 2019. The recruitment began on Dec.15, 2019, and the approximate date when recruitment will be completed is about Dec. 31, 2023.

## Data Availability

The participant-level data set cannot be made publicly available because of Chinese data protection rules and regulations. The statistical code is available upon request.

## Abbreviations

POCD: Postoperative cognitive dysfunction
POD: Postoperative delirium
AD: Alzheimer’s disease
GCP: Good clinical practice
CAM: Confusion Assessment Method
TICS-m: Telephone interview for cognitive status—modified
CRF: Case report form
SPIRIT: Standard Protocol Items: Recommendations for Interventional Trials
MMSE: Mini-Mental State Examination
WMS: Wechsler Memory Scale
